# Chinese herbal medicine for the treatment of cough variant asthma: a study protocol for a double-blind randomized controlled trial

**DOI:** 10.1186/s13063-018-3073-x

**Published:** 2019-01-03

**Keywords:** Chinese herbal medicine, Cough variant asthma, Randomized controlled trial

## Abstract

**Background:**

Cough variant asthma (CVA) is one of the leading causes of chronic coughing. The main treatment is currently anti-inflammatory medication. However, the coughing may return or be aggravated and lung function may deteriorate once the anti-inflammatory treatment is stopped. The effect of Chinese herbal medicine (CHM) on chronic coughing is remarkable, but high-quality evidence supporting its effectiveness is still lacking. This trial aims to evaluate the safety and efficacy, especially the long-term efficacy, of CHM plus anti-inflammatory medications for the treatment of CVA.

**Methods/design:**

A randomized placebo-controlled double-blind trial will be conducted. It will consist of a 3-month intervention followed by a 6-month follow-up period.

The target sample size is 60 patients with CVA who are between 18 and 70 years old. The eligible subjects will be allocated randomly into the experimental or control group in a ratio of 1:1. Patients in the experimental group will take CHM granules (4.9 g twice daily), while patients in the control group will be given a matched placebo. An administration of salmeterol/fluticasone propionate combination for 12 weeks will be the basic therapy for the two groups. The primary outcome is the cough visual analog scales (CVAS). The secondary outcomes include quality of life, rate of symptom relapse, lung function, and blood tests. A safety assessment will also be performed during the trial.

**Discussion:**

The evidence gathered by the trial will be a valuable addition to informing treatment options for patients with CVA.

**Trial registration:**

http://www.chictr.org.cn, ID: ChiCTR-IOR-16009148. Registered on 3 September 2016.

**Electronic supplementary material:**

The online version of this article (10.1186/s13063-018-3073-x) contains supplementary material, which is available to authorized users.

## Background

Cough variant asthma (CVA) is the most common cause of chronic cough [1–3]. According to a Chinese epidemiological survey, CVA accounts for 1/3 of cases of chronic cough [4]. In Japan, this proportion reaches 42.2% [5]. Long-term and constant coughing seriously affects the quality of life of patients with CVA. Such patients tend to be more depressed and anxious than classic asthma outpatients, on average [6]. Currently, maintenance therapy with a combination of inhaled corticosteroid and long-acting β2-agonist (ICS/LABA) is recommended for the treatment of CVA [7–9]. After discontinuing the anti-inflammatory treatment, cough symptom scores may increase, and lung function and eosinophilic airway inflammation may become aggravated and return to their baseline levels. The cumulative relapse rate of symptoms is as high as 67% after discontinuing treatment for 6 months [7].

Chinese herbal medicine (CHM) is widely used for CVA in China. It is reported that CHM plus ICS/LABA is better at reducing cough symptom scores, improving lung function, and improving quality of life compared with ICS/LABA alone [10–12]. Studies have also suggested that CHM plus ICS/LABA could further reduce levels of serum inflammatory factors, such as IL-10, IL-17, and IL-4/IFN-γ, compared to treatment with ICS/LABA alone [13, 14]. Furthermore, CHM plus ICS/LABA is better at reducing levels of airway neurotransmitters in the sputum than ICS/LABA alone [11]. Another study showed that compared to ICS/LABA alone, CHM plus ICS/LABA was superior at inhibiting airway remodeling in patients with CVA [15]. Although many clinical studies have proven that CHM plus ICS/LABA is superior to ICS/LABA alone for the treatment of CVA, the methodological quality of these studies was low because of the absence of sample size calculations, lack of definite random methods, unclear use of blinding methods, and so on. Furthermore, in only one study did participants undergo a follow-up period after stopping treatment [12]. How do cough symptoms, lung function, and airway inflammation change after stopping treatment with CHM plus ICS/LABA? Do these outcomes show a greater improvement after treatment with CHM plus ICS/LABA compared to after treatment with ICS/LABA alone? These questions remain to be determined.

A CHM prescription that was developed by [name] consists of ephedra (*mahuang*), asarum (*xixin*), fructus schisandrae (*wuweizi*), folium eriobotryae (*pipaye*), radix peucedani (*qianhu*), pummelo peel (*huajuhong*), folium perillae (*zisuye*), radix sileris (*fangfeng*) and radix asteris (*ziwan*). From the theory of traditional Chinese medicine, this prescription can warm the lungs, dispel wind, relieve coughing, and reduce the production of sputum. Most Chinese herbs in the prescription have been proven to be useful in the treatment of asthma. For example, it has been proven that the effective components of ephedra (*mahuang*) can decrease the secretion of IL-5, IL-13, and IL-8, alleviate the infiltration of eosinophils in the bronchoalveolar lavage fluid, inhibit airway remodeling, and inhibit the proliferation of airway smooth muscle cells [16–19]. Asarum (*xixin*) and fructus schisandrae (*wuweizi*) are often used in combination in Chinese medicine. Animal experiments have shown that the effective components of these two herbs may prolong the coughing latent period and decrease coughing frequency [20]. An extract of fructus schisandrae can also increase antioxidant levels and reduce oxidative damage. This also suggests that it may be helpful in the treatment of asthma [21]. It has been reported that folium eriobotryae (*pipaye*) has anti-inflammatory and immunoregulatory effects [22, 23]. An injection of folium eriobotryae can reduce the number of CD4+ cells, enhance the function of CD8+ cells, and regulate the CD4+/CD8+ imbalance [24]. The Th17/Treg cell balance has recently been discovered to be important in the pathogenesis of asthma. It has been reported that radix peucedani (*qianhu*) can alleviate airway inflammation and reduce airway hyperresponsiveness by regulating the imbalance of Th17/Treg cells [25]. In China, pummelo peel (*huajuhong*) is one of the most widely used Chinese herbs for respiratory diseases. Animal experiments have shown that pummelo peel can eliminate phlegm and relieve coughing, while also having anti-inflammatory, antioxidant, and immunomodulatory effects [26–29]. In addition, the other herbs in the prescription, folium perillae (*zisuye*), radix sileris (*fangfeng*), and radix asteris (*ziwan*), have anti-inflammatory effects as well. In general, the prescription may alleviate the symptoms or causes of asthma in multiple ways.

Based on a review of the literature and clinical observation, we predicted that our prescription plus ICS/LABA may be better at relieving coughing, improving lung function, and alleviating airway inflammation compared to ICS/LABA alone, even after the discontinuation of treatment. An observational study with a small sample size of 20 was carried out at a respiratory outpatient department. The control group was treated with ICS/LABA, while the experimental group was treated with ICS/LABA plus CHM. During the 12-week treatment period, the cough visual analog scales (CVAS) decreased from 5.13 ± 1.42 (mean ± standard deviation) to 1.21 ± 0.93 in the control group and from 5.11 ± 1.10 to 0.8 ± 0.69 in the experimental group. However, at the end of the 24-week follow-up phase, the CVAS increased to 4.50 ± 2.72 in the control group and 2.36 ± 2.54 in the experimental group. In addition, the cumulative percentages of patients whose symptoms worsened were 60% in the control group and 20% in the experimental group at the end of the follow-up period. We observed that ICS/LABA plus CHM was better for the treatment of CVA than ICS/LABA alone, not only during the 12-week treatment phase but also during the 24-week follow-up phase. Therefore, we have designed a randomized controlled trial to evaluate the long-term efficacy and safety of CHM plus ICS/LABA for the treatment of CVA.

## Methods/design

### Study design

This is a single-center double-blind randomized controlled trial. The trial has been approved by the Institutional Ethics Committee of Guangdong Provincial Hospital of Chinese Medicine (GPHCM; B2016–097-01) and registered in the Chinese Clinical Trial Registry (ChiCTR-IOR-16009148). The trial aims to investigate the additional benefit and safety of oral CHM compared to salmeterol/fluticasone propionate combination (SFC) alone for the treatment of CVA, with special consideration of long-term efficacy. This study protocol conforms to the Standard Protocol Items: Recommendations for Interventional Trials guidelines (Fig. 1 and Additional file 1).

**Fig. 1 Fig1:**
[figure not shown]
Spirit figure

### Trial procedure

The entire trial consists of a screening assessment, a 2-week run-in period (weeks −2 and −1), a 12-week treatment period (weeks 1 to 12), and a 24-week follow-up period (weeks 13 to 36) (Fig. 2).

**Fig. 2 Fig2:**
[figure not shown]
Trial flow chart. CHM Chinese herbal medicine, SFC salmeterol/fluticasone propionate combination

Potential participants will be invited to an initial assessment (first visit) consisting of screening for inclusion and exclusion criteria. If eligible, participants will be asked for informed consent and will undergo assessments of CVAS and quality of life, as well as a full blood count, blood tests on kidney and liver function, an electrocardiogram, and a chest radiograph examination. Then they will commence a 2-week run-in period. During this period, the participants’ use of asthma-related medication and CHM will be restricted. Participants will be provided with a salbutamol inhaler (Ventolin 5 mg/ml, GlaxoSmithKline, UK), to be used as required during this period to ease coughing until the treatment period begins. In the 2-week run-in period, the participants will be required to record the severity of their cough each day using the CVAS. After the run-in period, participants will undergo another set of baseline assessments (second visit), including assessments of quality of life, lung function, and blood tests.

After the baseline assessments, participants will be randomly allocated to receive 12 weeks of CHM plus SFC or placebo plus SFC. CVAS will be self-reported by the participants and recorded daily in a diary during the treatment period. Face-to-face assessments with blinded assessors will be scheduled at weeks 4 (third visit), 8 (fourth visit), and 12 (fifth visit). These will collect additional data, including lung function assessments and blood tests, as well as evaluations of quality of life, safety, and drug usage. Participants will be interviewed by telephone at weeks 2, 6, and 10 to determine adherence to the medication regulations and to report adverse events (AEs). The frequency of visits and phone calls can be increased if necessary.

During the 24-week follow-up phase, participants will continue to record CVAS daily in their diaries and document their utilization of health resources (including drug therapy use). They will attend follow-up assessments at weeks 24 and 36 (sixth and seventh visits). At each visit, quality of life, lung function, AEs, and drug usage will be assessed and participants will undergo blood tests.

### Participants

The participants will be recruited from the respiratory outpatient department of GPHCM. Poster, newspaper, and Internet advertisements will also be used for recruitment. Participants will be included only if they satisfy all the following inclusion criteria: (1) the diagnostic criteria for CVA [9], (2) between 18 and 70 years of age, and (3) CVAS ≥ 2.

Patients with one or more of the following conditions will be excluded: (1) systematic corticosteroid treatment, bronchodilator treatment, or CHM treatment in the last 4 months; (2) serious acute or chronic organic disease or mental disorder; (3) pregnant, breastfeeding, or planning a pregnancy; (4) known sensitivity to the intervention drugs of the trial; and (5) participating in other trials or participation in a trial within the last month.

### Interventions

#### Experimental group

The oral CHM granule will be produced by Tian Jiang Pharmaceutical Co., Ltd. (Jiangyin, Jiangsu, China). The herbs in the prescription will be mixed, cooked, filtered, and pressure spray-dried to form granules. The granules will be packaged into small single-dose sachets, each weighing 4.9 g. Participants in the experimental group will take two sachets twice a day for 12 weeks, dissolving each dose in warm boiled water. At the same time, patients will take SFC (50/250 μg, GlaxoSmithKline, England) twice a day for 12 weeks.

#### Control group

Placebo granules will be produced and packaged by the same manufacturer. They will consist of starch with no active ingredients. The placebo will be matched as closely as possible in appearance and taste to the real granules by adding various edible pigments. The dosage and administration of the placebo and SFC will be the same as in the experimental group.

### Randomization, allocation concealment, and blinding

Eligible patients will be randomly allocated into the experimental group or the control group in a ratio of 1:1 through the central web-based interactive randomization service system run by GPHCM. A block randomization procedure will be performed by the Key Unit of Methodology in Clinical Research at GPHCM using SAS 9.2 software (SAS Institute Inc., Cary, USA).

The allocation will be concealed until the trial has closed and the analysis has completed. The patients, investigators, outcome assessors, and statisticians will not know the intervention allocation. The randomization schedule and blinding codes will be kept strictly confidential until the statistical analysis has completed. Blinding will be ensured by using a matched placebo granule identical in color, shape, and taste to the intervention granule. The quality of the CHM granule and the matched placebo will be rigorously controlled according to Chinese good manufacturing practices, and will be tested and verified by the researchers.

### Outcome measures

#### Primary outcome

The primary outcome is CVAS change from baseline to the end of the follow-up phase (week 36). CVAS is used to assess the participants’ perceptions of the severity of their cough. Participants will be asked to draw a vertical line intersecting a 10-cm horizontal line to indicate the severity of their cough: zero is no cough while 10 cm is the worst cough imaginable [30].

#### Secondary outcomes

##### Quality of life

The total score in the Chinese version of the Leicester Cough Questionnaire [31] will be used to assess the quality of life of the participants (at weeks 1, 4, 8, 12, 24, and 36).

##### Lung function

Lung function will be determined mainly by measuring the forced expiratory volume in the first second (FEV1), the ratio of forced vital capacity occupied by forced expiratory volume in the first second (FEV1/FVC), and cumulative dose of bronchial activator to reduce FEV1 by 20% (PD20-FEV1) (at weeks 1, 12, 24, and 36).

##### Blood tests

The blood tests will include peripheral blood eosinophil count, eosinophil cationic protein, IgE, IFN-γ, and IL-4 (at weeks 1, 12, 24, and 36).

##### Other secondary outcomes

The rate of symptom relapse will be assessed at week 36. Overall health resource utilization will be recorded, including doctor visits, hospitalizations, and medication usage.

### Safety assessment

Blood and urine samples, liver function, renal function, electrocardiograms, and chest X-rays will be examined at the end of the run-in period and at weeks 4 and 12. Researchers will pay attention to abnormal changes in the results.

An AE is any adverse medical event that occurs during the trial, regardless of whether it is related to the drugs of the trial. Patients will be required to report all AEs at each visit. The effects, degree, time of occurrence, duration, treatment process, and follow-up of AEs will be recorded on case report forms. All AEs will be reviewed to assess the causal effects of the interventions, according to the standards set by the Uppsala Monitoring Centre of the World Health Organization [32].

### Termination and withdrawal

The trial will be terminated for any participant who develops one or more of the following conditions during the trial: (1) CVA develops into typical asthma, (2) intolerable side effects, or (3) serious acute or chronic organic disease. Any participant can withdraw from the trial for any reason at any time without prejudicing current or future treatments. The investigators will try to contact any withdrawn or terminated participants to complete the final assessment. Reasons for withdrawal or termination and the last medication time will be recorded. All withdrawn and terminated cases will be reported and analyzed.

### Compliance

The compliance evaluation will be conducted using the pill counting method. Each participant will be asked to keep a daily medication diary. Investigators will telephone the participants every 2 weeks to check their compliance. At the subsequent visit, the participants will show the investigator their diaries and report their compliance with the doctor’s advice. Ongoing support, such as free registration and treatment advice, will be provided to the participants in the follow-up phase.

### Sample size estimation

The sample size calculation for the primary outcome needs to be statistically and clinically significant. Based on previous literature [7] and our observational study, a sample size of 24 participants in each group can achieve 90% power to dismiss from a two-sided type I error of 0.05 to detect a superiority margin difference of 2.5 in this trial with two-tailed *P* values < 0.05 indicating significance. The total sample size was adjusted to 30 participants in each group to allow for 20% loss to follow-up and non-compliance.

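### The stated 90% power is for a difference of 2.5 with no SD given; at the 2.14 seen in the plan's own pilot, the SD that reproduces it gives about 79% with 24 per group

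*Protocol article*

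**What the plan says.** Under Sample size estimation, the protocol article says that "a sample size of 24 participants in each group can achieve 90% power", with a "two-sided type I error of 0.05", "to detect a superiority margin difference of 2.5 in this trial". The inputs are described only as "Based on previous literature [7] and our observational study". No SD is given. The allowance for attrition follows: "The total sample size was adjusted to 30 participants in each group to allow for 20% loss to follow-up and non-compliance".

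The observational study is reported in the Background. It had 20 patients. Baseline CVAS was 5.13 (SD 1.42) on control and 5.11 (SD 1.10) on experimental treatment. At the end of the 24-week follow-up "the CVAS increased to 4.50 ± 2.72 in the control group and 2.36 ± 2.54 in the experimental group". No SD of change and no correlation between baseline and follow-up is reported.

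Under Primary outcome: "The primary outcome is CVAS change from baseline to the end of the follow-up phase (week 36"). Under Statistical analysis, changes from baseline are compared between groups by analysis of variance, with two-tailed P < 0.05 as the criterion.

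**The concern.** The sample-size statement cites the pilot as a basis, yet the difference it is powered for is about 17% larger than the pilot difference (2.5/2.14 = 1.17), and no reason is given. Two further things are unclear. The SD is not stated, so a reader cannot tell whether it belongs to the week-36 score or to the change that is the primary outcome. And 2.5 is called a superiority margin, although the planned test is of zero difference.

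At stake is how a null result is read. Long-term benefit is the trial's central question. A non-significant result set against a claimed 90% power would look like stronger evidence against a benefit than it is, if the true effect is near what the pilot showed.

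**Working it through.** **Inputs.** From Sample size estimation: n = 24 per group, two-sided alpha 0.05, power 90%, difference 2.5, 20% loss. From Randomization: 1:1. From the Background: the pilot means and SDs above.

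**Pilot difference.**
- Week-36 score: 4.50 − 2.36 = 2.14.
- Change from baseline: (5.11 − 2.36) − (5.13 − 4.50) = 2.75 − 0.63 = 2.12.

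**Pooled week-36 SD.** √[(2.72² + 2.54²)/2] = 2.63.

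**Reproducing the plan's figure.** n = 2(1.96 + 1.2816)² × 2.63² / 2.5² = 23.3, rounded up to 24. Power at n = 24 is 90.8% by the normal approximation and 89.6% by the noncentral t. Attrition: 24/(1 − 0.2) = 30. A one-sided test with the same SD would give 19, so it does not reproduce.

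The SD implied by 24 per group, 90% and 2.5 is 2.67 (normal) or 2.62 (t). The pilot week-36 SD fits, but the match does not prove that it was used (see the change SD below).

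**Same SD, pilot difference** (noncentral t):

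| Difference | n per group | Power |
|---|---|---|
| 2.5 | 24 | 89.6% |
| 2.14 | 24 | 78.8% |
| 2.12 | 24 | 78.0% |
| 2.14 | 30 | 87.2% |

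For 90% power at 2.14 the same formula gives 31.8, so 32 per group; at 2.12 it gives 32.4, so 33.

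**SD of change.** Per arm, variance = SD₀² + SD₃₆² − 2r·SD₀·SD₃₆, then averaged over arms:
- Mean baseline variance: (1.42² + 1.10²)/2 = 1.613.
- Mean product of SDs: (1.42 × 2.72 + 1.10 × 2.54)/2 = 3.328.
- Change variance: 6.925 + 1.613 − 6.656r.

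This equals the week-36 variance when r = 1.613/6.656 = 0.24. The correlation r is an assumption, because the document gives none.

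**Power of ANOVA on change, n = 24** (noncentral t):

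| r | SD of change | Difference 2.5 | Difference 2.12 |
|---|---|---|---|
| 0 | 2.92 | 83% | 69% |
| 0.24 | 2.63 | 90% | 78% |
| 0.5 | 2.28 | 96% | 88% |

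**ANCOVA on run-in CVAS.** The residual SD is 2.63 × √(1 − r²), which never exceeds 2.63. With 45 degrees of freedom and n = 24, power at 2.5 is 89.6% at r = 0, 91% at r = 0.24 and 96% at r = 0.5. At 2.12 it is 78%, 80% and 88%.

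**The case against.** The strongest reply is that nothing has been miscalculated: 24, 90% and 30 all follow from a difference of 2.5 and an SD near 2.63. That stands. So does the reply that a target difference need not equal a pilot estimate. The plan cites literature as well as the pilot and says the calculation should be clinically as well as statistically significant, so 2.5 may come from that literature or be a clinically chosen value. The pilot cannot rule it out: assuming 10 patients per group, its 95% interval is 2.14 ± 2.10 × 2.63 × √(2/10), or −0.33 to 4.61. What does not stand is that the reader can tell any of this from the text.

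Three stronger readings are tempting, and the documents do not support them.

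- A reader might infer that the raw week-36 SD was wrongly used for a change endpoint. No SD is stated, and a change SD of the same size (r about 0.24) fits equally well. A raw SD would be optimistic for the change endpoint only below that correlation and conservative above it.
- A reader might say that the pilot's own figures give power as low as 69%. That needs r = 0, which the pilot does not report. At r = 0.5 the figure is 88%.
- A reader might take the word margin literally and conclude that the trial must show a difference above 2.5, which it would have almost no power to do. The same sentence speaks of detecting the difference with two-tailed P < 0.05, and the Statistical analysis section plans no test against a margin. The wording is loose; the test is not in doubt.

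It can also be said that the intention-to-treat analysis, with last observation carried forward, nominally includes all 30 per group, where power at 2.14 is 87%. That is fair, although imputed values and non-compliance could dilute the effect.

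**Conclusion.** The point holds in limited form. The 90% is right for a difference of 2.5 with an SD of about 2.63. It does not carry over to the effect in the pilot that the plan cites: at 2.14 and that SD, power is about 79% with 24 evaluable per group and 87% with 30. These figures assume that the pooled week-36 pilot SD applies, which is inferred from the match and not stated.

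For the analysis actually planned, ANOVA on change, power cannot be fixed from the document. Over r = 0 to 0.5 it runs from 83% to 96% at a difference of 2.5 and from 69% to 88% at 2.12.

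Severity is minor to moderate. The number of patients and the endpoint can stay as they are. What needs correcting is what the power statement promises and the label on 2.5, and the choice of analysis can remove most of the dependence on the unknown correlation.

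**What to change.** Keep 60 patients and make these changes.

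- Replace the term superiority margin difference with target difference, since the planned test is of zero difference.
- State the SD used, whether it refers to the week-36 score or to change, and where 2.5 comes from (cited literature, clinical importance, or both).
- If the SD is the pooled pilot value of 2.63, state power as about 90% for a difference of 2.5, and about 79% for the pilot difference of 2.14 with 24 evaluable per group (87% with 30).
- Analyse the primary outcome by ANCOVA adjusted for the run-in CVAS average in place of ANOVA on change. An SD of 2.63 is then conservative at any correlation, and about 90% power at 2.5 holds even at r = 0, where ANOVA on change gives 83%.

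The cost is wording plus a change in the primary model, which should be fixed before unblinding. The run-in CVAS is already collected, so no extra patients or data are needed. The price is a less favourable power statement.
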